### Main outcomes

The resolution of clinical symptoms and interpretation of laboratory assays will be assessed in the study groups.

Clinical symptoms:FeverDry coughShortness of breathHeadacheMyalgiaOxygen saturationMortality rate

Laboratory markers:C-reactive protein (CRP)Malondialdehyde (MDA)Total antioxidant capacity (TAC)White blood cell (WBC)Neutrophils countLymphocytes countThe ratio of neutrophils to lymphocytesLevels of 25 hydroxyvitamin D and magnesium

### Randomization

A computer-generated block randomization list is used for randomization. In this way, 24 blocks of 4 are made using codes A, B, C, and D, numbering from 1 to 24 (ABCD, ACBD, ABDC, ADBC, ACDB, ADCB, BACD, BCAD, BADC, BDAC, BCDA, BDCA, CABD, CBAD, CADB, CDAB, CBDA, CDBA, DABC, DBAC, DACB, DCAB, DBCA, DCBA) and then using R software, twenty-six blocks from blocks 1 to 24 are randomly selected as follows (3, 4, 7, 1, 2, 23, 11, 14, 18, 19, 6, 10, 6, 21, 17, 7, 9, 5, 22, 12, 20, 16, 13, 15, 3, 8). Allocated codes are then kept in sealed opaque envelopes, such that the numbers 1 to 104 are written on the envelopes and the codes A, B, C, and D are placed inside the envelopes as mentioned above order. For example, since block number 3 is the first choice, based on this block, the first person will receive treatment A, the second B, the third D, and the last will receive treatment C. This continues in the same way until 4 treatments are assigned to all patients.

### Blinding (masking)

Investigators and patients are blinded to group allocation and treatment. A double-blind design is achieved using matched placebos. Vitamin D and magnesium supplements and placebos are placed in the same package with codes of A, B, C, and D by a responsible person who is not aware of the study objectives. The code information will be given to the investigators after having done the statistical analysis. Moreover, to blind the participants, they are explained at the beginning of the study who will receive one of four types of intervention and will not be told the exact type of supplement.

Vitamin D supplements and placebos were provided by Zahravi Pharmaceutical Company (Iran). Magnesium placebos were made from starch with the same color and shape as magnesium supplements by the Faculty of Pharmacy of Hormozgan University of Medical Sciences.

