### Intervention and comparator

Participants will be randomly allocated to one of the four following groups: (A) vitamin D (two 50,000 IU capsules at the beginning of the study, two 50,000 IU capsules on the 4th day, one 50,000 IU capsule on the 11th day, and one 50,000 IU capsule on the 17th day) and magnesium supplement (300 mg/day); (B) vitamin D capsule and magnesium placebo; (C) magnesium supplement and vitamin D placebo; and (D) vitamin D placebo and magnesium placebo.

To ensure patient compliance with the assigned treatment, the subjects are monitored weekly by telephone and, if necessary, in-person visits. The compliance rate will be calculated according to the number of delivered and returned capsules by the following formula: number of capsules delivered − number of capsules returned/number of capsules delivered.

The criteria for discontinuation are any medical complications during supplementation or at the request of the patient. However, there is no possibility of harm to participants due to the type of dietary intervention. If the assigned intervention is discontinued for any reason, the patient has to be excluded from the study.

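### The protocol prints the full allocation order and labels packs with the four letters that define the arms, so the plan as written does not protect allocation concealment or investigator blinding

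*Protocol article*

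**What the plan says.** The protocol article claims masking of both sides in its Blinding (masking) section: "Investigators and patients are blinded to group allocation and treatment". That section describes the packs ("Vitamin D and magnesium supplements and placebos are placed in the same package with codes of A, B, C, and D") and says that the key stays closed: "The code information will be given to the investigators after having done the statistical analysis".

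Two other sections use the same four letters.

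- Intervention and comparator, like the abstract, ties each letter to a treatment. It begins "Participants will be randomly allocated to one of the four following groups: (A) vitamin D (two 50,000 IU capsules at the beginning of the study", with magnesium added in that arm, and continues "B) vitamin D capsule and magnesium placebo; (C) magnesium supplement and vitamin D placebo; and (D) vitamin D placebo and magnesium placebo".
- Randomization builds the list from those letters: "24 blocks of 4 are made using codes A, B, C, and D, numbering from 1 to 24". It writes out all 24 numbered blocks, then the 26 block numbers drawn, in order. Envelopes 1 to 104 are filled in that order. A worked example follows for the first block: "the first person will receive treatment A, the second B, the third D, and the last will receive treatment C".

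**The concern.** Concealment requires that the person who enrols a patient cannot know the next assignment. Investigator blinding requires that those who treat, assess and analyse cannot tell which arm a patient is in. Here the realised sequence and a legend for the letters stand in the investigators' own document, while the masking statement says that the key is withheld from them. Opaque envelopes conceal nothing from someone who has the list of their contents.

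Knowledge of the next assignment permits selective enrolment. Knowledge of a patient's arm can colour how staff elicit and record cough, breathlessness, headache and myalgia. It can also influence decisions that this text leaves to judgement: removal after treatment is stopped, and the choice of covariates for the mixed model.

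Two further features weaken protection even if the list were secret. The block size is fixed at four. One code is shared by a whole arm, and no patient-specific pack number is described.

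**Working it through.** **Step 1. Reproduce the list.** Inputs, all from Randomization: the 24 numbered blocks, and the draw, of which the first half is 3, 4, 7, 1, 2, 23, 11, 14, 18, 19, 6, 10, 6 and the second half is 21, 17, 7, 9, 5, 22, 12, 20, 16, 13, 15, 3, 8.

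- The 24 blocks are exactly the 4! = 24 distinct orders of A, B, C, D.
- Replacing each drawn number by its block gives: ABDC ADBC BACD ABCD ACBD DBCA BCDA CBAD CDBA DABC ADCB BDAC ADCB DACB CBDA BACD BADC ACDB DCAB BDCA DBAC CDAB CABD CADB ABDC BCAD.
- Length: 26 × 4 = 104. Each block holds each letter once, so there are 26 of each. Both figures agree with the stated sample size.
- The first block, number 3, is ABDC, as in the protocol's worked example.

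The code in every envelope is therefore readable: 104 of 104.

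**Step 2. From code to treatment.** Intervention and comparator gives A = both supplements, B = vitamin D with magnesium placebo, C = magnesium with vitamin D placebo, D = both placebos. If pack letter A is group A, and so on, all 104 treatments are readable as well. The worked example speaks of receiving treatment A, which supports this reading. No sentence states that the two sets of letters are the same.

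**Step 3. If the pack key is scrambled.**

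- The next letter is still known from the list for all 104 envelopes, but its meaning is not.
- One code covers one arm, so learning one patient's treatment reveals 26 of 104 patients.

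**Step 4. If staff do not have the list but see and track earlier codes.** Within a block of four different letters, the chance of naming the next letter correctly is 1/4 for the first position, 1/3 for the second, 1/2 for the third and 1 for the fourth.

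- Average: (1/4 + 1/3 + 1/2 + 1) / 4 = 2.083 / 4 = 0.521.
- Expected correct: 104 × 0.521 ≈ 54, against 104 × 1/4 = 26 with no information.
- Certain in advance: the last position of each block, 104 / 4 = 26.

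| What staff hold | Next letter named correctly | Treatment known |
|---|---|---|
| Nothing | 25% | no |
| Past codes and block size | 52% (26 of 104 certain) | only if the letters match the arms or an arm has been unmasked |
| Printed list, scrambled key | 100% | only for an arm that has been unmasked (26 patients each) |
| Printed list, letters match the arms | 100% | 104 of 104 |

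**The case against.** The best defence is that a person separate from the investigators coded the packs and that the key is said to be closed until after the analysis. On that view the letters in the arm descriptions may be mere list numbering, and a recruiter who knows that the next code is C learns nothing useful. This stands in part. The match of letters is an inference, so full knowledge of treatment is conditional, and the 52% and 26 of 104 figures concern letters, not treatments. It does not rescue the plan, because the letters are used throughout without any sign of re-mapping and the sequence itself is printed.

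Three stronger readings are tempting and are not supported.

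- *Double-blinding fails altogether.* Matched placebos are described, patients are not told which supplement they receive, and laboratory and data-entry staff are stated to be blinded. MDA, the sample-size variable, is a laboratory measure. What is exposed is concealment from investigators who hold the list, and their blinding.
- *Recruiters had the list.* The article is dated 6 February 2023, after the anticipated end of recruitment in August 2022, and the full protocol is a separate file that is not shown. Publication alone exposes no recruiter. Equally, the article still calls recruitment ongoing and does not say who held the list.
- *Measuring 25(OH)D and magnesium breaks the blind.* Levels by code can hint at the arms in any supplement trial that measures them. Outcomes are taken only at baseline and 3 weeks, so post-treatment values bear mainly on the analyst and not on enrolment. This is a secondary point, not a contradiction in the text.

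**Conclusion.** The concern holds against the plan as written. The printed sequence gives the code of all 104 envelopes to anyone with the protocol, and the shared letters make the treatments readable too if pack and arm letters coincide. That conflicts with the statement that the code is withheld until after the analysis. With a scrambled key, the code sequence remains fully known and a single unmasking exposes an arm of 26. Without the list, the fixed blocks still raise correct guessing of the next letter from 25% to 52%, provided that staff see and track earlier codes.

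The documents do not show that anyone used the list, that unblinding occurred, or that patients, laboratory staff or data-entry staff were unmasked.

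**What to change.** **Patients not yet randomised, if any.** Label packs with unique numbers in place of four shared letters. Generate a new list held only by someone outside the investigator team, and keep the realised sequence out of the protocol. Varied block sizes are preferable. If recruitment ended as anticipated, this part no longer applies.

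**Patients already randomised.** Give the analyst freshly scrambled neutral arm labels, unrelated to the letters in the protocol. Withhold the 3-week 25(OH)D and magnesium results until the other outcomes are locked. Baseline values cannot be withheld, because eligibility depends on them (exclusion above 80 ng/ml and 2.6 mg/dl). State in the trial report who had access to the list and when, and whether the pack letters matched the arm letters.

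**Cost.** Minor relabelling and a new list for any remaining patients, one re-coded dataset, and a later merge of two assays. Sample size and the analysis model are unaffected.

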### Sample size

A total of 104 COVID-19 patients aged 18 to 65 admitted to the Shahid Mohammadi hospital in Bandar Abbas, Iran, who are eligible for the study are recruited. They are randomly divided into four groups of 26 subjects.

Based on the findings of the previous study [18], the sample size was calculated by the G*Power software, where the effect size for MDA variable was 0.68, alpha error probability was 0.05, power = 0.8, number of groups = 4, number of measurements = 2, and the assumed correlation among the repeated measures was 0.5. Then, taking into account the dropout rate of 0.1, the sample size in each group was estimated to be 26 patients.

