### Statistical analysis

The Kolmogorov–Simonov test will be used to check the normality of variable distribution. One-way ANOVA and Bonferroni post hoc tests will be used to analyze the differences between groups.

The mixed linear model will be used to estimate the treatment effect and the possible confounding variables will be adjusted in the model. IBM SPSS version 22 will be used for statistical analysis. *P*-value ≤ 0.05 will be considered a significant level in all statistical tests. To handle protocol non-adherence, the intention-to-treat (ITT) principle will be used to analyze data based on the original treatment assignment of the patients. Variables will be expressed as mean ± standard error or 95% confidence interval. The research team will not conduct interim analyses to stop or extend the trial because of the low-risk nature of the nutritional intervention in the present study. Indeed, early detection of the study hypotheses is unlikely and early termination of the intervention is not supposed to have any additional protection for patients.

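### The printed G*Power inputs do not give 26 patients per group, and the 80% power is not tied to the comparisons the trial plans to make

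*Protocol article*

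**What the plan says.** The Sample size section of the protocol article takes its effect size from a previous study and names G*Power. On the effect size and significance level it says: "the effect size for MDA variable was 0.68, alpha error probability was 0.05". The remaining inputs are a target power of 80%, four arms, two time points and a within-patient correlation of 0.5. It concludes: "taking into account the dropout rate of 0.1, the sample size in each group was estimated to be 26 patients". That makes 104 in total.

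It does not say whether 0.68 is Cohen's f or a standardised difference d, nor which effect (between groups, within patients, or their interaction) was powered.

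The Statistical analysis section then states: "One-way ANOVA and Bonferroni post hoc tests will be used to analyze the differences between groups". It adds a mixed linear model, adjusted for confounders, to estimate the treatment effect. The Trial design section describes the four arms as a factorial design.

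**The concern.** The inputs and the result are printed side by side, so the result can be checked. If it cannot be reproduced, the only power statement in the article has no known basis, and a reader cannot tell whether the trial is several times larger than its own calculation required or about the right size for a smaller effect.

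There is also a question of what the 80% refers to. The listed inputs describe one overall F test across four groups and two time points, whereas claims about individual arms would come from Bonferroni pairs. If MDA shows no difference, someone will want to cite 80% power to detect 0.68. Whether that is fair depends on what 0.68 measures and on which comparison it was meant for.

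**Working it through.** **Inputs** (Sample size section): effect size 0.68, alpha 0.05, power 0.80, k = 4 groups, m = 2 measurements, ρ = 0.5, dropout 0.1. Stated result: 26 per group.

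**Formulas.** Power comes from the noncentral F with 3 and N − 4 degrees of freedom, where N is the total and the noncentrality λ is as G*Power defines it:
- Between factors: λ = f² × N × m / (1 + (m − 1)ρ) = f² × N × 1.333
- Within-between interaction: λ = f² × N × m / (1 − ρ) = f² × N × 4

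Dropout is applied as n / 0.9, rounded up.

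**0.68 taken as f**, the effect size this routine asks for (f² = 0.4624):
- Between: N = 24 gives λ = 14.80 and power 0.845; N = 20 gives only 0.744. So 6 per group, and 6 / 0.9 = 6.7, i.e. 7.
- Interaction: N = 12 gives λ = 22.20 and power 0.880. So 3 per group, and 3 / 0.9 = 3.3, i.e. 4.

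With 92 evaluable (23 per group; 26 × 0.9 = 23.4), power for f = 0.68 exceeds 0.999 in either test.

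**0.68 taken as d, with f = d / 2 = 0.34** (f² = 0.1156):
- Between: N = 76, λ = 11.71, power 0.808. So 19 per group, 22 after dropout.
- Interaction: N = 28, λ = 12.95, power 0.804. So 7 per group, 8 after dropout.
- One-way ANOVA, or the Cohen-type effect-size option (λ = f²N): N = 100. So 25 per group, 28 after dropout.
- SPSS-type option (λ = f²(N − 4)): N = 104. So 26 per group before dropout, 29 after.

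**Smaller f on the d reading.** If 0.68 is the largest difference between any two arms, f depends on where the other arms lie. It is 0.34 with two arms at each extreme, 0.68 × √3 / 4 = 0.294 with one arm apart from three equal arms, and 0.68 / (2√2) = 0.24 with two arms at the midpoint. Between factors, these give 22, 28 (N = 100) and 42 (N = 148; 37 / 0.9 = 41.1) per group after dropout. Solving backwards, f = 0.305 gives N = 92, i.e. 23 per group, and 23 / 0.9 = 25.6, i.e. 26.

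**Pairwise power with 23 evaluable per arm.** Noncentral t, noncentrality d × √(n / 2), 88 degrees of freedom, six pairs at 0.05 / 6 = 0.0083:
- If 0.68 is a pairwise d: 0.68 × √11.5 = 2.31. Power is 0.35 with Bonferroni and 0.63 unadjusted.
- If 0.68 is f: the largest pair differs by at least 2f = 1.36 SD, and Bonferroni power is at least 0.97. Adjacent arms with equally spaced means differ by 0.61 SD, with power 0.27.

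**Factorial main effect.** Each factor compares 46 with 46 evaluable patients, noncentrality d × √23, two-sided 0.05:
- 0.59 SD: 2.83, power 0.80.
- 0.68 SD: 3.26, power 0.90.

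**The case against.** The best case for the plan has three parts.

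First, the article is a summary. The previous study and the full protocol (Additional file 1) are not shown, and either may settle whether 0.68 is f or d and which G*Power option was used. That is fair as far as omissions go. It does not cover a printed result that disagrees with the printed inputs.

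Second, 26 is not out of reach. On the d reading f can lie anywhere from 0.24 to 0.34, and 0.305 within that range gives exactly 26. This rules out any claim that no reading leads to 26. But 0.305 is obtained by solving backwards from 26; the article states neither that value nor a pattern of means that implies it.

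Third, a repeated-measures calculation with two time points is a reasonable counterpart to a mixed model on baseline and three-week data, and the article never attributes its 80% to a pairwise test. This stands. The Statistical analysis section names no single decisive test, so it would be wrong to say the power calculation belongs to an analysis that is not planned.

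A reader might also infer that the trial is underpowered, with 35% in place of 80%. The article does not support that: the 35% requires 0.68 to be a pairwise d, whereas the listed inputs point to f, and on that reading the largest pair is well powered.

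**Conclusion.** The stated 26 per group does not follow from the stated inputs. Taken at face value they give 7 or 4 per group after dropout. With 0.68 halved to f = 0.34 they give 22 or 8 in the repeated-measures routine, and 28 or 29 under a one-way or alternative effect-size option. This rests on G*Power's usual noncentrality definitions and equal group sizes.

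One possible cause, by inference only, is that the between-factors total of 24 was read as a per-group number: 24 × 1.1 = 26.4 and 24 / 0.9 = 26.7, either of which becomes 26 if rounded down. Nothing in the article confirms it.

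The 80% is the power of an omnibus repeated-measures F test and should not be carried over to the Bonferroni pairs. Pairwise power may be well below or well above 80%, depending on what 0.68 means and how the four means are arranged. Neither a shortfall nor an excess can be asserted until that is stated. The number recruited is not itself shown to be inadequate: for a factorial main effect of 0.68 SD, 104 patients with 10% dropout give about 90% power.

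**What to change.** Keep 104 patients and rewrite the paragraph:
- State whether 0.68 is f or d, how it was derived from the previous study, and which G*Power test and effect were used.
- Correct the calculation so that the inputs lead to the result, or say plainly that 104 was fixed on other grounds.
- State what 104 delivers for the factorial analysis. With 46 against 46 evaluable, there is 80% power at two-sided 0.05 for a main effect of about 0.59 SD in MDA, and about 90% for 0.68 SD, before any gain from baseline adjustment. These figures describe the fixed sample size; they do not show that such effects are plausible.
- If any power is quoted for the pairwise comparisons, give it separately, at the Bonferroni level and for a stated difference.

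The cost is one reworded paragraph, with the same text carried into the full protocol if it holds the same calculation. No extra patients and no change to conduct.

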### Statistical analysis

The Kolmogorov–Simonov test will be used to check the normality of variable distribution. One-way ANOVA and Bonferroni post hoc tests will be used to analyze the differences between groups.

The mixed linear model will be used to estimate the treatment effect and the possible confounding variables will be adjusted in the model. IBM SPSS version 22 will be used for statistical analysis. *P*-value ≤ 0.05 will be considered a significant level in all statistical tests. To handle protocol non-adherence, the intention-to-treat (ITT) principle will be used to analyze data based on the original treatment assignment of the patients. Variables will be expressed as mean ± standard error or 95% confidence interval. The research team will not conduct interim analyses to stop or extend the trial because of the low-risk nature of the nutritional intervention in the present study. Indeed, early detection of the study hypotheses is unlikely and early termination of the intervention is not supposed to have any additional protection for patients.

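### Plain Bonferroni over the six arm pairs is valid but more conservative than the 5% limit requires; a Shaffer step-down rejects at least as much at the same family-wise error

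*Protocol article*

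**What the plan says.** The Statistical analysis section of the protocol article names one procedure for comparing the arms: "One-way ANOVA and Bonferroni post hoc tests will be used to analyze the differences between groups". The 0.05 level "will be considered a significant level in all statistical tests". The next paragraph adds a mixed linear model, adjusted for confounders, to estimate the treatment effect.

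The Sample size section gives the planning inputs: "the effect size for MDA variable was 0.68, alpha error probability was 0.05, power = 0.8, number of groups = 4". It adds that "the assumed correlation among the repeated measures was 0.5" and reaches 26 per group after "taking into account the dropout rate of 0.1".

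Three things are not written: how many pairs are compared, the level used for each pair, and whether the pairs are tested only after a significant F test. Six pairs at 0.05/6 follows from four groups and the word Bonferroni.

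**The concern.** Bonferroni divides 0.05 by six at every step, as if all six equalities could still be true after some have been rejected. With four means that is impossible. The pairwise tests therefore run well below the 5% family-wise limit whenever some arms really differ. In a trial with 23 to 26 patients per arm, pairwise power is modest under a plausible reading of the planning effect, so giving some of it up has a price. Questions such as combination versus single agent, or each arm versus double placebo, are pairwise questions and are tested this way.

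**Working it through.** **Inputs.** Four arms (Sample size), hence 4 × 3 / 2 = 6 pairs. Level 0.05, taken as two-sided. 26 per arm, or 26 × 0.9 = 23.4, about 23, after dropout. Effect 0.68, read first as a standardised difference d between two arms. Normal outcome and equal variances are assumed. The correlation of 0.5 does not alter the result: the variance of a change score is 2σ²(1 − 0.5) = σ², the same as for the end value.

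**The plan's own figure.** The 26 per group could not be reproduced under the readings tried. With 0.68 as Cohen's f, the between-group and one-way tests need 7–8 per group after dropout. With f = 0.34 they need 22 and 28. A two-group comparison with d = 0.68 needs 34 before dropout. So the stated sample size does not settle whether 0.68 is d or f. That is a separate matter, but it means both readings must be shown here.

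**How many equalities can be true.**

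| Pattern of four means | True pairwise equalities |
|---|---|
| all equal | 6 |
| three equal, one apart | 3 |
| two and two | 2 |
| one equal pair, two others apart | 1 |
| all different | 0 |

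If at least one, two or three equalities are false, at most three are true. If four are false, at most two are true. If five are false, at most one is true. This gives divisors 6, 3, 3, 3, 2, 1 for the ordered p-values, or thresholds 0.0083, 0.0167, 0.0167, 0.0167, 0.025, 0.05. If a 5% F test must reject first, that test has already dealt with the all-equal case, and the first divisor may also be 3.

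**Bonferroni power for one pair.** Noncentral t with 4n − 4 degrees of freedom and noncentrality d√(n/2):
- n = 23: 0.68 × √11.5 = 2.31, critical t 2.70 on 88 df, power 35.3%.
- n = 26: 0.68 × √13 = 2.45, critical t 2.69 on 100 df, power 40.9%.

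**Power for a pair differing by 0.68, where 0.68 is the largest difference between any two arms** (simulation, pooled variance, rounded):

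| Pattern | n per arm | Bonferroni → step-down, no F condition | Bonferroni → step-down, both only after F |
|---|---|---|---|
| one arm apart | 23 | 35% → 41% | 35% → 43% |
| two and two | 23 | 35% → 42% | 35% → 44% |
| other two arms midway | 23 | 35% → 37% | 34% → 39% |
| one arm apart | 26 | 41% → 47% | 41% → 49% |
| two and two | 26 | 41% → 48% | 41% → 50% |
| other two arms midway | 26 | 41% → 43% | 40% → 45% |

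With one arm apart or a two-and-two split, the step-down at 23 per arm (41–42%) about matches Bonferroni at 26 (41%).

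**If 0.68 is Cohen's f.** With the other two arms midway, the extreme pair differs by 0.68 × √8 = 1.92. Power is then practically 100% under either rule, and the gain is nil for that pair.

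**Family-wise error.** Bonferroni without the F condition gives about 4.1% when all arms are equal, 2.2% when one arm differs and 1.7% for two and two. Requiring F first changes only the all-equal figure, to 3.8%. Both step-down versions stayed at or below 5% in every pattern, including very large effects. A flat 0.05/3 with no F condition does not hold: about 7.7% when all arms are equal.

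**The case against.** The strongest reply is that nothing here is wrong. Bonferroni after ANOVA is standard and holds family-wise error at or below 5% in every configuration. Choosing among valid procedures is partly taste. The step-down gives no matching simultaneous intervals, although the plan reports 95% intervals, and its adjusted p-values have to be worked out from the unadjusted ones. The treatment effect is estimated separately by the mixed model. All of this stands, and it limits the point to an optional gain in efficiency.

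A reader might infer more, and three stronger readings are not supported:
- **That the plan corrects twice, because an F test always comes first.** The words post hoc suggest that order, but the protocol does not make the pairs conditional on F. If they are tested regardless, the first divisor must stay at 6.
- **That about 8–10 points of power are lost.** This is not general. Figures near that size need the F condition, 0.68 read as d, and one arm apart or a two-and-two split; about ten points needs each agent to add 0.68, so that combination and double placebo differ by 1.36. With the other arms midway, the gain is about 5 points after F and 2 without.
- **That the larger divisor buys no protection.** This is true only against the 5% limit. Realised error is about half when one arm differs (2.2% against roughly 4.3%).

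**Conclusion.** The point holds as an inexpensive improvement. Bonferroni over six pairs is valid but stricter than the plan's 5% limit needs. With 0.68 as a standardised difference between two arms, and no larger difference between any pair, the step-down gains about 2–7 points of pairwise power without an F condition and about 5–9 points with one. The low end applies when the other arms lie midway. The gain is close to nil for the extreme pair if 0.68 is Cohen's f. The results assume normal outcomes, equal variances and two-sided tests. The logic of the divisors does not depend on the effect size. Only the ANOVA pairwise comparisons are affected.

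**What to change.** In the Statistical analysis section, replace the Bonferroni tests with this rule: the six unadjusted pairwise p-values are ordered from smallest to largest and compared in turn with 0.05 divided by 6, 3, 3, 3, 2 and 1, stopping at the first that fails (Shaffer step-down). This needs no F test and can only add rejections to those Bonferroni makes.

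If the investigators prefer to test pairs only after a significant overall F test at 0.05, the plan should say so explicitly, and the divisors 3, 3, 3, 3, 2, 1 may then be used. A flat 0.05/3 without that condition must not be used.

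The cost is one sentence and a short hand calculation from the p-values of the same ANOVA, with no change to patients or data. Pairwise intervals would be shown unadjusted or as Tukey intervals (critical value 2.62 against 2.70 for Bonferroni at 88 df, so still narrower). Realised family-wise error moves closer to 5% but stays within it. The Blinding section releases the treatment codes only after the analysis, so the change can be made without knowledge of treatment if the analysis has not yet been run. The sentence giving the effect size should also say whether 0.68 is d or f.

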### Data collection

At baseline, general characteristics of patients including age, gender, medications used, and underlying chronic diseases are collected by investigators using a paper-based record system. All outcomes of interest (clinical symptoms and laboratory markers) are assessed at baseline and at the end of the intervention period (3 weeks later).

Data entry will be done by one of the blind research team members and a double check is performed by another blinded team member. Written informed consent is collected for each patient at the beginning of the study by investigators. Dietary supplements and biochemical tests are provided free of charge for participants to increase their willingness to participate in the study. Data protection was done by keeping the identity of the patients anonymous by excluding their names throughout the study.

After an overnight fast (10–12 h), 10 ml venous blood samples are taken from patients in the morning. First, 4 ml blood is collected in ETDA tube (1 mg/ml) and used for complete blood cell (CBC) count. The remaining 6 ml blood is allowed to clot for 45 min at room temperature; serum is then isolated by centrifugation at 3000 rpm for 10 min and stored at – 70 °C until analysis. Blood samples are collected and assayed by lab investigators that are blinded to the patient assignments.

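### For continuous outcomes the deciding between-group analysis should adjust for baseline: the one-way ANOVA cannot, and the plan does not say that the mixed model does

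*Protocol article*

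**What the plan says.** The Statistical analysis section of the protocol article names two analyses for the comparison of groups. The first is a one-way ANOVA with Bonferroni post hoc tests, assigned to the differences between groups. It does not say whether the response is the week-3 value or the change from baseline. The second is given in one sentence: "The mixed linear model will be used to estimate the treatment effect and the possible confounding variables will be adjusted in the model". The form of that model is not given, nor whether the baseline enters as a covariate or as one of two repeated outcomes. Neither analysis is called primary.

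Two other sections bear on this. Data collection states: "All outcomes of interest (clinical symptoms and laboratory markers) are assessed at baseline and at the end of the intervention period", three weeks later. Sample size plans on "number of groups = 4, number of measurements = 2" and adds that "the assumed correlation among the repeated measures was 0.5". So the baseline values will exist, and the planning treats them as informative about the week-3 values.

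**The concern.** In a randomised comparison of a continuous outcome measured before and after treatment, the baseline value is usually the best single predictor of the follow-up value. Conditioning on it removes the part of the week-3 variance that the baseline explains. A one-way ANOVA on week-3 values leaves that part in the error term. A change score subtracts the baseline with a fixed coefficient of 1 rather than the estimated one, and at a correlation of 0.5 this gains nothing.

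The trial has 26 patients per arm before dropout. If the ANOVA is taken as the deciding test, precision that has already been paid for is lost. Because the article does not say which analysis decides, the same data can also give two answers to the same question, with different standard errors.

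**Working it through.** **Inputs from the protocol article.** Sample size: "alpha error probability was 0.05", power 0.8, "the effect size for MDA variable was 0.68", "number of groups = 4, number of measurements = 2", correlation r = 0.5, dropout 0.1, 26 per group (104 in total). Trial design: 1:1:1:1 allocation, factorial, so each main effect compares 52 with 52.

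**Assumption, not in the document.** A main effect of 0.5 SD, used only to turn variance into power.

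**The plan's own figure.** The stated 26 per group could not be reproduced from these inputs.
- Reading 0.68 as Cohen's f, the four-group repeated-measures between-factors test needs 6 per group (7 after dropout) and the interaction test 3 (4).
- Reading it as a standardised difference d, so that f = 0.34, the between-factors test needs 19 (22) and a plain one-way ANOVA 25 (28).

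That is a separate matter. The result below uses only the correlation, not the 26.

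**Step 1: variance of a group contrast, relative to a single week-3 measurement** (equal variances at both times, complete data).
- ANOVA on week-3 values: 1.
- ANOVA on change, or an unconstrained two-time-point group-by-time contrast, which estimates the same quantity: 2(1 − r) = 2 × 0.5 = 1.0.
- ANCOVA, or a mixed model with baseline means constrained equal: 1 − r² = 1 − 0.25 = 0.75.

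At r = 0.5 the adjusted analysis therefore has 25% less variance than either form of the ANOVA. The standard error falls by 1 − √0.75 = 13%. In patients, 104 / 0.75 = 138.7, so an unadjusted trial would need about 139 to match. A simulation with 26 per arm and 20,000 replicates gave variance ratios of 0.757 against week-3 values and 0.761 against change, close to the formula.

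**Step 2: other correlations.**

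| r | ANCOVA / week-3 ANOVA (1 − r²) | Reduction | ANCOVA / change ((1 + r)/2) | Reduction |
|---|---|---|---|---|
| 0.3 | 0.91 | 9% | 0.65 | 35% |
| 0.4 | 0.84 | 16% | 0.70 | 30% |
| 0.5 | 0.75 | 25% | 0.75 | 25% |
| 0.6 | 0.64 | 36% | 0.80 | 20% |
| 0.7 | 0.51 | 49% | 0.85 | 15% |

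**Step 3: gain over the planned mixed model.** Its form is not stated, so only the ends of the range can be given at r = 0.5.
- Baseline as a covariate, or baseline means constrained equal: about 0%.
- Unconstrained group-by-time contrast: 25%.

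**Step 4: illustration in power** (two-sided 0.05, noncentral t, difference 0.5 SD, adjusted SD = √0.75).
- 52 versus 52: 71% unadjusted, 83% adjusted. The effect detectable with 80% power falls from 0.56 to 0.48 SD.
- After 10% dropout, 52 × 0.9 = 46.8, taken as 47 versus 47: about 67% unadjusted, 79% adjusted.

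**The case against.** The strongest reply is that the article assigns estimation of the treatment effect to the mixed linear model, not to the ANOVA, and that planning on two correlated measurements suggests the baseline was meant to be used. If that model conditions on baseline, it already has the 0.75 variance and nothing is gained over it. This stands. A reader might infer that the plan as a whole discards the baseline and loses 25%. The document does not support that, because the mixed model's form is not stated. The 25% holds against the ANOVA, in either form, and against an unconstrained group-by-time contrast.

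A reader might also infer that covariates will be picked once the data have been seen. The article does not say when they are chosen. A list of covariates is detail that a condensed article may leave to the full protocol or analysis plan, and the Blinding section withholds the meaning of the codes until the analysis is done. Coded groups do not rule out data-driven choice, but there is no basis here for saying that it is planned. Nor does it follow that all other adjustment should be removed. Prognostic covariates can add precision for the same reason as the baseline does, provided they are fixed in advance.

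Three limits on the size also stand. The correlation of 0.5 is a planning assumption. The 0.5 SD effect and the two-group main-effect contrast are illustrations, not the four-group Bonferroni comparison that the article describes. And baseline adjustment of this kind suits continuous outcomes only.

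What the reply does not remove is that one-way ANOVA is a stated method, assigned to the between-group comparison, and cannot carry a covariate. The article does not make it subordinate to the mixed model.

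**Conclusion.** The point holds in limited form. The article tests group differences by a method that cannot adjust for baseline. It does not say that the accompanying mixed model does so, or which of the two decides, although the baseline values are collected and a correlation of 0.5 is assumed.

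For continuous outcomes such as MDA, CRP, TAC, cell counts and oxygen saturation, the stake is a variance reduction of about 25% if r = 0.5, measured against the ANOVA or an unconstrained group-by-time contrast. Against the planned mixed model it lies between about 0% and 25%, depending on a specification that is not given. The comparison rests on equal variances at the two times and complete data. The trial remains valid either way: what is at issue is unused precision and an undecided choice between two analyses.

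**What to change.** In the Statistical analysis section, replace the one-way ANOVA as the deciding analysis of continuous week-3 outcomes. Suggested wording:

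*Each continuous outcome at week 3 will be analysed by ANCOVA (or by a mixed linear model with baseline means constrained equal across groups), with terms for vitamin D, magnesium, their interaction and the baseline value of that outcome. This model decides. Any further covariates are listed before the data are examined.*

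If the mixed model was always meant to take this form, it is enough to say so and to state that it, not the ANOVA, decides. The change does not apply to mortality, which has no baseline value, or to symptoms recorded as yes or no.

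The cost is wording and one degree of freedom for the baseline term. The data are already to be collected, and the SPSS package named in the plan fits the ANCOVA.
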